### Statistical considerations

Linear mixed-effects modeling will be used to evaluate effect of interventions over time on the primary and key secondary outcomes. The models incorporate subject-specific random effects to account for within-subject correlation due to repeated measures. Group averages, as well as subject-specific intercepts and slopes, will be estimated to capture potential variations in the baseline values and slopes among individuals. Linear mixed-effects models accommodate missing data due to dropout, such that all randomized participants can be included. We will compare participants who complete the study with those who do not and identify potential factors that are associated with dropout {20c}. In the mixed-effects models, we will adjust for time-invariant covariates (age at randomization, sex) and time-varying covariates (muscle strength, lean mass, muscle OXPHOS capacity, VO2max). By including these indices of “muscle quality” as covariates in the models, we will be able to assess whether intervention effects are explained by these effects. To assess other potential factors influencing outcomes, we will also analyze the incremental effect of adding each of the other measured covariates (final dose of NR achieved, final training intensity achieved) to the models.

The primary outcome for our study is the change in muscle strength (quadriceps extension, Z-score) from baseline to 16 weeks. We expect exercise and NR to each produce an increase (relative to control/placebo) with respect to the primary outcome of muscle strength from baseline to week 16. We posit that the effects of exercise and NR in combination will be additive and possibly even synergistic. Despite our strategies to track and optimize adherence, it is possible that the change in Z-score will vary across participants in response to one or both interventions. We will fit a linear model with the outcome of change in Z-score of muscle strength and covariates of treatment arm and baseline Z-score. Using a modification of previous strategies for the analysis of factorial designs, the family-wise Type I error rate is maintained at < 5% by using a two-stage approach: a Holm-Bonferroni correction is applied in Stage 1, and a single contrast is pre-specified in Stage 2 [43]. In Stage 1, we will test if the mean Z-score in each of the 3 active treatment arms differs from control (no-exercise + placebo). In Stage 2, if the exercise + NR arm differs from the control arm, we will then compare exercise + NR to exercise alone, to determine whether NR increases mean Z-score beyond the effect of exercise alone; 95% confidence intervals will be determined for each effect of interest.

In secondary analyses, we will seek to identify disease covariates and physiological factors (e.g., low muscle OXPHOS capacity at baseline) that are associated with treatment response [44]. With respect to additional outcomes, we anticipate that strength in other muscle groups, lower extremity muscle mass (measured via DXA), and muscle OXPHOS capacity (measured via CrCEST), will all increase in response to both interventions, and in statistical models will demonstrate independent contributions to the observed increases in muscle strength (primary outcome) and other key outcomes. In addition, blood metabolomics will show correlates of increased OXPHOS capacity (e.g., decreased acylcarnitine related to improved fatty acid oxidation capacity, organic acid profiles consistent with increased TCA cycle anaplerosis, and increased CoA species). Even if we do not detect changes in response to either of these interventions, our mechanistic assessments will produce an integrated understanding of the factors associated with low muscle mass, strength and OXPHOS in HCT survivors. The safety data will be an ancillary benefit to guide clinicians caring for HCT survivors who may be considering taking this supplement. The primary analysis will be repeated with each secondary outcome. Additional models will explore whether change from baseline can be explained by either baseline demographic or clinical covariates (age at randomization, sex, key clinical characteristics such as anthracycline and/or steroid exposure, age at HCT, TBI, GvHD grades II-IV, interval since HCT, and hypogonadism) or features of the intervention (final dose of NR, final training intensity in Mets per week). We will explore interactions between key variables and treatment arm. With respect to sex, we will include sex by treatment interactions in the model and explore the results of individual sex-stratified analyses, though we may lack adequate power to detect sex-specific differences {12}.

In addition, we expect exercise and NR to each produce an increase (relative to control/placebo) with respect to the secondary outcome of VO_2_max. We expect that the effects of exercise and NR in combination will be additive, and possibly even synergistic. The effect of sex will also be assessed. The analysis for VO_2_max Z-score (Aim 2) will be the same as for Aim 1, since both outcomes are expressed as a Z-score. We will fit a linear model with the outcome of change in Z-score of VO_2_max and covariates of treatment arm and baseline Z-score for VO_2_max {8} {20a}.

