**Methods/design:**

We will perform a randomized controlled trial testing 16 weeks of in-home aerobic and resistance exercise and NR in AYA HCT survivors, with a primary outcome of muscle strength via dynamometry and a key secondary outcome of cardiovascular fitness via cardiopulmonary exercise testing. We will also test the effects of these interventions on i) muscle mass via dual energy x-ray absorptiometry; ii) muscle mitochondrial OXPHOS via an innovative non-invasive MRI-based technique, and iii) circulating correlates of NAD^+^ metabolism via metabolomics. Eighty AYAs (ages 15-30y) will be recruited 6–24 months post-HCT and randomized to 1 of 4 arms: exercise + NR, exercise alone, NR alone, or control. Outcomes will be collected at baseline and after the 16-week intervention.

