## Methods/design

In this randomized controlled trial, we will prospectively enroll 80 participants status-post HCT at two sites, the Children’s Hospital of Philadelphia (CHOP) (Philadelphia, PA, USA) and the City of Hope Medical Center (COH) (Duarte, CA, USA). There will be 4 arms: exercise intervention with NR supplementation, exercise intervention with placebo, no exercise intervention with NR supplementation, and no exercise intervention with placebo. The individualized exercise intervention will occur in the home, overseen remotely via Telehealth by exercise intervention physiologists from St. Jude Children’s Research Hospital (Memphis, TN, USA) {9}. Participants who are randomized to the exercise intervention will be given the necessary equipment to participate either before they depart the site or by mail. Each participant will take part in the study for 16 weeks, with a total of three onsite in-person visits: one at baseline, one interim visit at week 8, and a final visit at the end of the 16-week intervention.

The primary objective of this study is to measure the effect of combination administration (NR + exercise) on skeletal muscle quality (strength along with mitochondrial OXPHOS capacity) in AYA HCT survivors {7}. Skeletal muscle quality will be measured by dynamometry, while OXPHOS capacity will be assessed through creatine chemical exchange saturation magnetic resonance imaging (CrCEST MRI). The secondary objective of this study is to measure the effect of combination administration (NR + exercise) on aerobic capacity (VO_2_max), as determined by cardiopulmonary exercise testing (CPET).

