### Study assessments {18a}

All study participants will complete a review of medical history, have their vital signs measured, and have laboratory assessments (CBC, CMP, HbA1c, lipid profile, blood to be banked for future ancillary metabolic and/or hormonal studies) (Table 3). Activity monitoring will be reviewed for seven days via an activity monitor (ActiGraph wGT3X-BT; ActiGraph Corp., Pensacola, FL) and, if assigned, the exercise training orientation will occur. After all study procedures are completed, supplement/placebo (NR/placebo) will be provided to the participant along with instructions and administration log. Specific to the primary and secondary outcomes, all participants will undergo the following assessments at the baseline and follow-up visits:

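### Two different analyses are assigned to the primary outcome and not ranked, and the subject-specific slopes of one are not identified if strength is measured only at baseline and week 16

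*Protocol article*

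**What the plan says.** All of this is in the protocol article.

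- **First model (Statistical considerations, first paragraph).** "Linear mixed-effects modeling will be used to evaluate effect of interventions over time on the primary and key secondary outcomes". On its structure: "Group averages, as well as subject-specific intercepts and slopes, will be estimated". On missing data: "Linear mixed-effects models accommodate missing data due to dropout, such that all randomized participants can be included". The same paragraph adjusts these models for age, sex and time-varying measures. Those measures include lean mass, OXPHOS capacity, VO2max and muscle strength, which is the primary outcome itself.
- **Second model (same section, second paragraph).** "The primary outcome for our study is the change in muscle strength (quadriceps extension, Z-score) from baseline to 16 weeks", and for this outcome "We will fit a linear model with the outcome of change in Z-score of muscle strength and covariates of treatment arm and baseline Z-score". The Holm-Bonferroni stage and the single second-stage contrast are attached here. The last paragraph of the section repeats this model for VO2max.
- **Ranking.** None is given. The third paragraph says that the primary analysis will be repeated for each secondary outcome, without saying which model that is.
- **Timing.** The abstract says "Outcomes will be collected at baseline and after the 16-week intervention". Methods/design lists three on-site visits: "one at baseline, one interim visit at week 8, and a final visit at the end of the 16-week intervention". Study assessments says "all participants will undergo the following assessments at the baseline and follow-up visits". The schedule of procedures (Table 3) is not reproduced in the text at hand.
- **Sample size.** Sample size and power plans to randomise 80 so that 64 (16 per arm) have complete data.

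**The concern.** The two models are not two descriptions of one analysis. They differ in who is analysed, in how baseline is handled and in what is adjusted for. With no ranking, there are two routes to the primary p-value, and the choice between them could be made after the results are known. The protection against dropout is claimed for one model, while error control and sample size are set for the other. A reader cannot tell whether the confirmatory test will use all randomised participants or only those with a week-16 value.

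A second question is whether the data can support the individual slopes that the mixed model is said to deliver. With two measurements per person, a departure of that person's slope from the group slope cannot be told apart from measurement error.

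**Working it through.** **1. The plan's own figure.** 64 / (1 − 0.20) = 80, which reproduces the number randomised. It counts people with complete data, which fits the change-score model and not an analysis of all 80.

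**2. The two models side by side.**

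| | Mixed model | Linear model of change |
|---|---|---|
| Participants | all randomised (80 planned) | those with a week-16 value (64 planned) |
| Baseline strength | an outcome record; no constraint on arm means stated | covariate |
| Other covariates | age, sex, post-randomisation measures | none |
| Multiplicity procedure | not attached | attached |
| Missing-data statement | attached | not attached |

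The analysis sets differ by 80 − 64 = 16 people, or 20% of those randomised.

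**3. Identifiability with two visits.** Code time as 0 and 1. Let a be the intercept variance, b the slope variance, c their covariance and s the residual variance. The data inform three moments:

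- baseline variance: a + s
- covariance: a + c
- week-16 variance: a + b + 2c + s

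That is three equations for four unknowns. Two solutions with the same moments:

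- (a, b, c, s) = (1.0, 0.5, −0.2, 0.3): 1.0 + 0.3 = 1.3; 1.0 − 0.2 = 0.8; 1.0 + 0.5 − 0.4 + 0.3 = 1.4
- (a, b, c, s) = (0.9, 0.3, −0.1, 0.4): 0.9 + 0.4 = 1.3; 0.9 − 0.1 = 0.8; 0.9 + 0.3 − 0.2 + 0.4 = 1.4

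The slope variance is 0.5 in one and 0.3 in the other, and no data at two visits can separate them. With week 8 added there are six moments for four parameters, and the model is identified.

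**4. What is and is not affected.** One data set was simulated with 80 randomised and 64 complete (80 + 64 = 144 records), and the correlated intercept-and-slope model was fitted by REML with four optimisers. All reached the same log-likelihood (−168.7066). The residual variance ran from 0.167 to 0.203 and the slope variance from 0.086 to 0.158. The arm-by-time effects were the same each time: 1.060, 0.193 and 1.582. The baseline-adjusted linear model on the 64 completers gave 1.043, 0.145 and 1.537. These are simulated values and only illustrate the point.

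**5. Precision.** Assume equal variances σ² at both visits, correlation ρ, dropout at random, known covariance, n = 20 randomised and m = 16 complete per arm, and no post-randomisation covariates. The variance of the estimated effect per arm is proportional to:

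- baseline-adjusted model: σ²(1 − ρ²)/m
- mixed model with free baseline means: σ²[(1 − ρ²)/m + (1 − ρ)²/n]

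The ratio of standard errors is √[1 + (m/n)(1 − ρ)/(1 + ρ)], with m/n = 16/20 = 0.8:

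- ρ = 0.5: √(1 + 0.8 × 0.5/1.5) = √1.267 = 1.125
- ρ = 0.7: √(1 + 0.8 × 0.3/1.7) = √1.141 = 1.068
- ρ = 0.86: √(1 + 0.8 × 0.14/1.86) = √1.060 = 1.030

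The article gives no ρ, so these values are assumptions that show a range.

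**The case against.** The strongest reply is that the confirmatory route can be recognised. Only the linear model carries the contrasts, the multiplicity procedure and the confidence intervals. It is the model restated for VO2max, and the sample size counts completers. The covariate-adjusted mixed models are partly described as a way to see whether muscle measures explain the intervention effects, which is an explanatory aim. This stands as the more natural reading. It does not settle the matter, because the section's opening sentence gives the mixed model to the primary outcome by name. A conflict between two stated models is also more than detail left to an analysis plan.

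On identifiability, a reader might infer that the mixed model cannot be fitted, will not converge, or gives a treatment p-value that depends on software defaults. The documents do not support that. The treatment effects depend on the total covariance of the two measurements, which is identified; only its split into components is not. Some software may warn or stop, but the missing-data claim is not attached to a model that is unusable for the arm comparison. The article also states no covariance structure for the random effects. With intercept and slope assumed uncorrelated there are three parameters for three moments, and the model is just identified, though by a constraint that the article does not mention.

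The two-visit premise is not certain either. There is a week-8 visit, assessments are placed at follow-up visits in the plural, and the schedule table cannot be seen. Dynamometry at week 8 would remove the identifiability part. The abstract points the other way, and no visible text places strength testing at week 8.

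A reader might also put the precision loss at √[2/(1 + ρ)], that is 15%, 8% and 4%. That formula holds when both models use the same people, and the mixed model has 16 further baselines. Those baselines alone add little information about change, so the 20% difference in analysis set should not be read as a 20% gain in information.

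**Conclusion.** Wrong as written. Two different models are assigned to the primary outcome and are not ranked, and the missing-data statement belongs to the one that carries neither the error control nor the sample size. This part holds whatever the visit schedule.

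The second part is conditional. If strength is measured only at baseline and week 16, a correlated random intercept and slope cannot be separated from residual error, so the variance components and subject-specific slopes are arbitrary. The arm-by-time effects remain estimable.

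The cost in precision of using the mixed model is modest: about 12.5%, 6.8% and 3.0% in the standard error at ρ of 0.5, 0.7 and 0.86. It rests on free baseline means, which the article neither states nor rules out, on the assumed ρ and on the planned 20% attrition. The main harm is the open choice of primary analysis, not a large loss of power.

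**What to change.** - In Statistical considerations, name the linear model of change on arm and baseline Z-score as the single primary analysis for muscle strength, and the same model for VO2max. State its analysis set.
- Replace the random-intercept-and-slope model with an identifiable longitudinal model as the supporting missing-data analysis. One suitable form has categorical visit, a baseline mean common to all arms and an unstructured within-person covariance. It would use all randomised participants with any value and no post-randomisation covariates. Other identifiable forms would also serve.
- Keep models with time-varying muscle measures for the explanatory question, and label them exploratory.
- If strength is measured at week 8, say so and include it as a visit.

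The cost is wording only: no new data, visits or participants. The choice should be fixed before unblinding.

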**Discussion:**

We expect that exercise with NR will produce larger changes than exercise alone in key outcomes, and that changes will be mediated by increases in muscle OXPHOS. We will apply the insights gained from this trial to develop individualized, evidence-supported precision initiatives that will reduce chronic disease burden in high-risk cancer survivors.

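### The mixed models said to evaluate the intervention effect, and to keep everyone randomised, adjust for variables that treatment is expected to change, and they are not ranked against the arm-plus-baseline model

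*Protocol article*

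**What the plan says.** Statistical considerations in the protocol article describes two models for the same outcomes.

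- **Mixed model (first paragraph).** "Linear mixed-effects modeling will be used to evaluate effect of interventions over time on the primary and key secondary outcomes". The paragraph says this approach accommodates dropout, so that nobody randomised need be left out. The models adjust for age and sex and for "time-varying covariates (muscle strength, lean mass, muscle OXPHOS capacity, VO2max"). The reason given is that "we will be able to assess whether intervention effects are explained by these effects". A further step looks at "adding each of the other measured covariates (final dose of NR achieved, final training intensity achieved) to the models". No version without the time-varying covariates is given, and the model is not labelled supportive or exploratory.
- **Linear model (second to fourth paragraphs).** "The primary outcome for our study is the change in muscle strength (quadriceps extension, Z-score) from baseline to 16 weeks". For it, "We will fit a linear model with the outcome of change in Z-score of muscle strength and covariates of treatment arm and baseline Z-score", and the Holm-Bonferroni Stage 1 tests and the single Stage 2 contrast follow. The third paragraph repeats this analysis for each secondary outcome. For aerobic capacity, "We will fit a linear model with the outcome of change in Z-score of VO_2_max and covariates of treatment arm and baseline Z-score for VO_2_max".

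The article also states that the covariates should respond to treatment. The Discussion part of the Abstract expects that "changes will be mediated by increases in muscle OXPHOS". The third paragraph of Statistical considerations predicts that both interventions will raise strength in other muscle groups, leg muscle mass and OXPHOS. The fourth predicts the same for VO2max.

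**The concern.** A covariate measured after randomisation and changed by treatment carries part of the treatment effect. Once it is held fixed, the arm coefficient no longer answers whether assignment to exercise or NR improved strength. It answers how much of the difference remains at equal lean mass, OXPHOS and VO2max. That is a direct effect, and randomisation does not protect it, because anything that influences both the covariate and the outcome can bias it in either direction.

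The same covariate list is given for every outcome. It contains strength, which is the primary outcome, and VO2max, which the Abstract calls the key secondary outcome. Taken literally, each would appear on both sides of its own model.

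The practical risk is conflicting answers. The trial could end with one estimate from the linear model and a smaller one, possibly of opposite sign, from the mixed model, with nothing in the text to say which is the treatment effect. The mixed model is also the only one presented as keeping everyone randomised, so a reader who wants the fuller analysis set is led to the mediator-adjusted result.

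**Working it through.** **Inputs from Sample size and power.** 80 randomised, 64 with complete data, 16 per arm, 20% attrition; 80% power for a 0.73 Z difference between exercise + NR and exercise alone.

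**Assumptions, not in the article.** Two-sided 5% level; SD of the change in strength Z-score; mediated shares; residual correlations. The only SD given is 1.4, for muscle-area Z-score, which is a different measure.

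**1. The plan's own figures.** 64 / (1 − 0.20) = 80, so N reproduces. The 80% power cannot be checked independently without an SD. Solving backwards, SD = 0.73 / [√(2/16) × (1.960 + 0.842)] = 0.737. With a t reference it is 0.725 (59 df) or 0.713 (30 df). About 0.72 is used below.

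**2. Adjusting for a mediator.** Let d be the total effect and s the share carried by the covariate. Given the covariate, the arm coefficient is d × (1 − s). This does not depend on the SD; the power does. Simulation: two arms of 16, ordinary least squares, one covariate shifted by 1 SD, 3,000 runs per row. Unadjusted, it returns about 0.73 with 78–80% power.

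| Share s | 0.73 × (1 − s) | Simulated coefficient | Simulated power |
|---|---|---|---|
| 0 | 0.73 | 0.73 | 69% |
| 25% | 0.55 | 0.54 | 47% |
| 50% | 0.37 | 0.37 | 30% |
| 75% | 0.18 | 0.18 | 15% |
| 95% | 0.04 | 0.04 | 7% |

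**3. Reading muscle strength as another muscle group.** If ankle or grip strength has the same treatment effect and SD, and residual correlation ρ with knee extension, the coefficient is 0.73 × (1 − ρ). For ρ = 0.3, 0.5, 0.7 and 0.9 this is 0.51, 0.37, 0.22 and 0.07 (simulated 0.52, 0.37, 0.22 and 0.08).

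**4. The outcome as its own covariate.** The fit is perfect, the covariate takes coefficient 1 and the arm coefficient is exactly 0.

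**5. No effect on strength, but the covariate responds.** If treatment shifts the covariate by k SDs, the arm coefficient is −ρ × k × SD. With SD 0.725:

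- ρ = 0.3: −0.11 Z (k = 0.5) and −0.22 Z (k = 1).
- ρ = 0.6: −0.22 Z and −0.44 Z. Two simulation runs gave −0.21 and −0.23, and −0.43 both times. The nominal 5% test rejected in 16–17% and 43–45% of data sets.

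The size is proportional to ρ, which the article does not give.

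**6. The two models side by side.** A change score needs a week-16 value, so without imputation the linear model uses roughly the 64 expected completers of 80. The mixed model is credited with using all 80. But a visit without the MRI or CPET value lacks a covariate and drops out unless it is imputed, which undercuts that advantage.

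**Limit.** The simulation uses two arms, one covariate and least squares. The plan has four time-varying covariates in a mixed model. The figures show the mechanism and its order of size; they do not predict this trial's result.

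**The case against.** The strongest reply is that the analysis that matters is clean. The primary outcome, the Holm-Bonferroni step and the Stage 2 contrast are all attached to a model with arm and baseline Z-score only, and the secondary outcomes and VO2max follow it. The total effect is therefore already specified. **This stands.** A reader might infer that the confirmatory test is compromised; the second to fourth paragraphs of Statistical considerations do not support that.

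Second, the first paragraph gives an explanatory purpose for the covariates, namely whether effects are explained by muscle quality. **This stands in part.** The purpose is stated, but the same models are also given the task of evaluating the intervention effect. One model conditioned on mediators cannot do both, and no unadjusted version accompanies it.

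Third, three stronger readings are tempting and go too far.

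- That the adjustment removes the treatment effect. It attenuates it; removal needs full mediation or self-adjustment.
- That strength is certainly regressed on itself. The list serves several outcomes, and an analyst would ordinarily drop the one being modelled. Strength could also mean other muscle groups, which the third paragraph treats as explanatory. The text does not say. Step 3 shows that this milder reading still attenuates the coefficient.
- That final NR dose and training intensity cannot be separated from arm at all. Dose varies by weight band within the NR arms, and the Exercise section expects heterogeneous progression. Both are nevertheless largely determined by arm: active dose is zero on placebo, and prescribed training exists only in the exercise arms.

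**Conclusion.** The point holds in a limited form. The article assigns to the mixed models the estimation of the intervention effect and the inclusion of everyone randomised, then conditions them on variables that it expects treatment to change. Their arm coefficient is a confoundable direct effect. The article does not rank this model against the arm-plus-baseline model.

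If the true effect is 0.73 Z and a covariate carries a quarter to three quarters of it, the mixed-model coefficient would be about 0.54 to 0.18 Z. That rests on 16 per arm, an SD of about 0.72 inferred from the stated power, and mediated shares that the article does not supply. The direction of the problem does not depend on those values as long as part of the effect runs through the covariates, which is what the article predicts.

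This is a stated rule, not a detail left to a fuller document. The error-controlled test is untouched. What is at risk is the interpretation of the mixed-model results and the freedom to choose between two estimates after the data are seen.

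**What to change.** In Statistical considerations:

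1. Name the linear model of change in Z-score on arm and baseline Z-score as the primary analysis, and state the role of the mixed model relative to it.
2. In any mixed model that estimates the intervention effect, allow only pre-randomisation covariates: baseline outcome, age, sex and site. Remove the time-varying covariates from it. It can then serve as the analysis that uses partial data from those who drop out.
3. Move lean mass, OXPHOS, VO2max and strength in other muscle groups to a separate mediation analysis, labelled exploratory and reported after the total effect. State that an outcome is never its own covariate and that the direct effect is not protected by randomisation.
4. Treat training intensity as an exploratory analysis within the exercise arms, and final NR dose as one within the NR arms. Read NR dose together with body weight, which sets it.

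The cost is wording only. No visit, measurement or participant is added, and the mechanistic question is kept. The change should be made before outcome data are seen by arm.

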### Sample size and power

With the proposed design, we have > 80% power to detect four scenarios of treatment-related changes in mean Z-score of 0.93–1.66 accounting for multiple testing with a family-wise Type I error rate < 5%. Notably, we have 80% power to detect a difference between exercise and exercise + NR (Scenario 1) of 0.73 Z-score. We have demonstrated that increases in muscle group specific strength of up to 100% (absolute amount) over 24 weeks are plausible, depending on the degree of initial deficits and muscle group tested [45]. In a 12-week pilot study, a mean increase of quadriceps strength of 14% was observed [46]. In a previous meta-analysis in adults, effect sizes of 0.53–0.79 were reported with supervised aerobic exercise [47, 48]. We anticipate that increases in the present study may be even larger for several reasons. First, these relatively young participants will have substantial muscle deficits, thus there is a clear opportunity to demonstrate benefit. Our preliminary data indicate muscle deficits in HCT survivors, with low Z-scores for muscle area (mean -0.9, SD 1.4). Also, we have chosen to intervene at the soonest potential opportunity post-HCT, thus we expect muscle deficits will be less established and participants will be more responsive to the interventions. Our team has considerable experience in supervising, individualizing, and adjusting the exercise regimen to achieve maximum benefit. Also, we will randomize 80 participants to achieve 64 (*n* = 16 in each of 4 arms) with complete data (i.e., conservatively allowing 20% attrition) {14}.

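### The assessment of whether muscle indices explain the strength gain mixes between-person and within-person associations, so cross-sectional correlation can pass for mediation of change

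*Protocol article*

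**What the plan says.** All references are to the protocol article.

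- **Model.** The first paragraph of Statistical considerations describes linear mixed models with random effects for each participant: "Group averages, as well as subject-specific intercepts and slopes, will be estimated". These models are adjusted for age and sex and for "time-varying covariates (muscle strength, lean mass, muscle OXPHOS capacity, VO2max".
- **Inference.** The same paragraph says that, by including these indices, "we will be able to assess whether intervention effects are explained by these effects". It does not mention centring, a within/between split or a change score for the indices.
- **Target.** The Discussion part of the Abstract expects that "changes will be mediated by increases in muscle OXPHOS". Later in Statistical considerations, the other muscle measures are expected to rise under both interventions and "in statistical models will demonstrate independent contributions to the observed increases in muscle strength".
- **Primary model.** This is stated separately: "We will fit a linear model with the outcome of change in Z-score of muscle strength and covariates of treatment arm and baseline Z-score". It contains no muscle index other than baseline strength.
- **Data.** The Methods/design part of the Abstract gives two outcome time points: "Outcomes will be collected at baseline and after the 16-week intervention". Sample size and power plans for 64 completers, 16 "in each of 4 arms) with complete data".

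**The concern.** The target is a within-person question: does a participant whose OXPHOS or lean mass rises also gain strength, and does that account for the arm effect? The stated method gives each index one coefficient. That coefficient is a weighted average of two slopes:

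- the between-person slope: participants with more muscle or better OXPHOS tend to be stronger at any visit, whatever the treatment;
- the within-person slope: a participant whose index rises gets stronger.

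Only the second bears on mediation of change. Subject-specific random effects do not separate the two. The same blended coefficient determines how far the arm effect shrinks when the index is added, so the apparent share explained carries the mixture too. Because the article expects both interventions to raise the indices, a coefficient that is purely cross-sectional would still remove part of the arm effect. The primary change-score model does not supply the missing test, since it holds only arm and baseline strength.

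At stake is the mechanistic conclusion, one of the two expectations announced in the Abstract's Discussion.

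**Working it through.** **Plan's own figures.** 64/(1 − 0.20) = 80, which reproduces the randomised sample size. The article gives no figure for the explanatory analysis, so its size has to be shown over assumed ranges.

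**Inputs from the article.** 64 completers in 4 arms of 16; outcomes at baseline and week 16; random intercepts and slopes.

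**Assumed inputs.** Between-person SD 1 and within-person SD σ = 0.5 (range 0.3-0.7) for strength and index. True within-person slope 0. Exercise raises the index by 0.5 and strength by 0.73; the article uses 0.73 as its detectable difference between exercise + NR and exercise alone, and here it is only a convenient effect size. ρ is the between-person correlation left after age and sex adjustment.

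**Formula.** With two visits and compound symmetry, take each participant's sum and difference over visits, each divided by √2. Apart from the arm effects:

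- variance of the index: A_S = 2 + σ² for the sum, A_D = σ² for the difference;
- covariance with strength: C = 2ρ for the sum, 0 for the difference;
- residual variances: R_S = A_S − 2bC + b²A_S and R_D = A_D(1 + b²);
- blended coefficient: b = (C/R_S) / (A_S/R_S + A_D/R_D), solved by iteration.

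**ρ = 0.5, σ = 0.5.** A_S = 2.25, A_D = 0.25, C = 1. The solution is b = 0.248: R_S = 2.25 − 0.496 + 0.138 = 1.892; R_D = 0.25 × 1.0615 = 0.2654; b = 0.5285/(1.189 + 0.942) = 0.248. The within-person slope is 0 and the between-person slope is 1/2.25 = 0.444, so the blend takes about 56% of the between-person slope.

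False share explained = b × shift in index / arm effect = 0.248 × 0.5/0.73 = 17%.

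**ρ = 0.3, σ = 0.5.** C = 0.6, R_S = 2.127, R_D = 0.2548; b = 0.2821/(1.058 + 0.981) = 0.138; share = 0.138 × 0.5/0.73 = 9.5%.

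**Simulation** (REML, 64 completers, two visits, true within-person slope 0, index shift 0.5):

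| ρ | False share explained | Blended term rejects at 5% | Within-person term rejects at 5% |
|---|---|---|---|
| 0 | about 0% | about 5% | 3-7% |
| 0.3 | 9-11% | 32-42% | 3-7% |
| 0.5 | 15-19% | 67-87% | 3-7% |

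The 5% level is assumed.

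**Random slopes.** A random intercept variance, a slope variance, their covariance and a residual variance make four parameters. Two visits identify three (two variances and one covariance), so an unstructured 2 × 2 covariance is the most that can be fitted. In a separate simulation with intraclass correlation 0.6-0.9, rejection under random intercept and unstructured covariance was 25-37% and 26-38% at ρ = 0.3, and 59-83% and 59-84% at ρ = 0.5. The random slopes do not remove the problem.

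**Larger shift.** If exercise raised the index by 1.0, the share at ρ = 0.5 would be 0.248 × 1.0/0.73 = 34%.

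**Opposite error.** With a true within-person slope of 0.5 and ρ = 0, power is 82% for the blended term and 96% for the within-person term.

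**The case against.** The strongest reply has four parts.

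1. **Silence on centring.** The article never says that the indices enter uncentred, and a condensed article may leave parameterisation to a fuller document. This stands in part: the undivided form is the plain reading, not an explicit statement. But the article does fix both the covariate form and the inference drawn from it, and no other model it describes separates the two associations.
2. **No test is stated.** The article speaks of assessing whether effects are explained and sets no null hypothesis or alpha. This stands. A reader might infer from the rejection rates that a false mediation claim is likely. The documents do not support that: the stated inference is most naturally about attenuation of the arm effect, where the false share is much smaller.
3. **The inputs are assumed.** No between-person correlation or intraclass correlation is given, and with no correlation there is no distortion. Because the models adjust for age and sex, and strength is an age- and sex-specific Z-score, the relevant correlation is a partial one and may be below the marginal one. This stands, and is why ranges are shown.
4. **The remedy has its own costs.** A two-visit deviation is more attenuated by measurement error than a level, and a participant with one visit adds nothing to it. This also stands, and the costs are listed with the fix.

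**Conclusion.** The point holds in a limited form. The stated method does not isolate the within-person association that the article wants to interpret, so part of any apparent explanation may be cross-sectional, and a real within-person effect may be understated. Under the assumptions above, the false share explained is about 9-11% at a between-person correlation of 0.3 and 15-19% at 0.5. It is nil at zero correlation and larger if the intervention moves the index more.

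Two stronger readings are not supported. One is that the model has random intercepts only: the article specifies intercepts and slopes, though with two visits the result is nearly the same. The other is that the efficacy conclusions are at risk: the primary comparisons use change in strength on arm and baseline Z-score, contain none of these time-varying indices, and are unaffected. This is a cheap and worthwhile correction to a mechanistic analysis, not a threat to the trial's main result.

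**What to change.** In the explanatory models only, replace each time-varying index (lean mass, OXPHOS, VO2max) by two terms: the participant's own mean over visits, and the deviation from that mean at each visit. Base any statement that an index explains or contributes to the strength gain on the deviation term, and report the person-mean term as a cross-sectional association. Keep an arm main effect in this model: the person mean contains the week-16 value, and the arm-by-time effect should rest on within-person change. Alternatively, in participants with both visits, regress change in strength on arm, baseline strength and change in the index.

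The cost is one sentence of analysis text and one further derived variable per index, with no new data. The downsides are:

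- some loss of precision if the between-person and within-person slopes are in fact equal;
- more attenuation from measurement error in a two-visit change;
- no within-person information from participants with a single visit (the plan allows for 20% attrition).

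The within-person term removes this one source of false evidence; it does not by itself establish causal mediation.
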